## Abstract

**Background:**

The early life gut microbiota are an important regulator of the biological pathways contributing toward the pathogenesis of noncommunicable disease. It is unclear whether improvements to perinatal diet quality could alter the infant gut microbiota.

**Objective:**

The aim of this study is to assess the efficacy of a perinatal educational dietary intervention in influencing gut microbiota in mothers and infants 4 weeks after birth.

**Methods:**

The Healthy Parents, Healthy Kids randomized controlled trial aimed to recruit 90 pregnant women from Melbourne, Victoria, Australia. At week 26 of gestation, women were randomized to receive dietary advice from their doctor (n=45), or additionally receive a dietary intervention (n=45). The intervention included an educational workshop and 2 support calls aiming to align participants’ diets with the Australian Dietary Guidelines and increase intakes of prebiotic and probiotic foods. The educational design focused on active learning and self-assessment. Behavior change techniques were used to support dietary adherence, and the target behavior was eating for the gut microbiota. Exclusion criteria were age under 18 years, diagnosed mental illnesses, obesity, diabetes mellitus, diagnosed bowel conditions, exclusion diets, illicit drug use, antibiotic use, prebiotic or probiotic supplementation, and those lacking dietary autonomy. The primary outcome measure is a between-group difference in alpha diversity in infant stool collected 4 weeks after birth. Secondary outcomes include evaluating the efficacy of the intervention in influencing infant and maternal stool microbial composition and short chain fatty acid concentrations, epigenetic profile, and markers of inflammation and stress, as well as changes in maternal dietary intake and well-being. The study and intervention feasibility and acceptance will also be evaluated as secondary outcomes.

**Results:**

The study results are yet to be written. The first participant was enrolled on July 28, 2016, and the final follow-up assessment was completed on October 11, 2017.

**Conclusions:**

Data from this study will provide new insights regarding the ability of interventions targeting the perinatal diet to alter the maternal and infant gut microbiota. If this intervention is proven, our findings will support larger studies aiming to guide the assembly of gut microbiota in early life.

**Trial Registration:**

Australian Clinical Trials Registration Number ACTRN12616000936426; https://www.anzctr.org.au/Trial/Registration/TrialReview.aspx?id=370939

**International Registered Report Identifier (IRRID):**

DERR1-10.2196/14771

## Introduction

### Background

The diversity and composition of the neonatal gut microbiota is garnering interest as a target for the prevention of noncommunicable diseases. The disappearing microbiome hypothesis contends that reduced bacterial diversity over generations results in increased allergic and metabolic disease risk in children [1]. In 1-month old infants, low microbial diversity is associated with an increased risk of later atopic eczema [2], allergic sensitization, allergic rhinitis, peripheral blood eosinophilia [3], and asthma [4]. In addition, differential microbial composition is associated with an increased risk of noncommunicable diseases, including allergic sensitization [3], eczema [2], asthma risk [5], neurodevelopmental outcomes [6], and later adiposity in infants [7]. Hence, novel methods of altering the neonatal gut microbiome are of interest. The influence of poor maternal diet (high fat or low fiber) on offspring gut microbiota has been studied in animals, demonstrating that poor maternal diets disturb offspring gut microbiota [8,9]. To our knowledge, there are no human randomized controlled trials (RCTs) with the primary aim of testing whether the maternal diet can modify the diversity and composition of the infant gut microbiota. Dietary supplementation trials of perinatal prebiotic or probiotic supplements provide a premise for testing this aim, with some studies indicating that these supplements modify the composition of gut microbiota in mothers [10] and infants [11,12]. Importantly, though, a supplementation approach fails to address the quality of the underlying diet. In humans, the prenatal diet has been associated with the composition of the infant gut microbiota [13,14], but it is still unclear whether this relationship is modifiable. Human studies are needed to determine whether infant gut microbiota can be modified through perinatal dietary change.

In murine [8] and primate [9] models, poor-quality prenatal diets disturb vertical transmission of microbiota (from mother to offspring). For example, a prenatal diet devoid of dietary fiber reduced microbial diversity and the abundance of fiber-degrading taxa in mothers and offspring [8]. Low diversity compounded over 4 generations and could not be corrected via a high-fiber diet. Similarly, compared with a low-fat prenatal diet (13% of energy from soya bean oil), a high-fat prenatal diet altered the microbiota of vaginally born primates [9]. This alteration was persistent at 1 year and could not be corrected by weaning offspring onto a low-fat diet [9]. In humans, compared with a low-fat prenatal diet (24% of daily energy from fat), a high-fat (43%) diet during pregnancy was associated with an altered infant gut microbiome, including a depletion of *Bacteroides* persisting to 4 to 6 weeks of age [13]. Taken together, these results suggest that poor-quality diets (such as low fiber, high saturated fatty acid, and high sugar content) during pregnancy and lactation disturb vertical transmission. However, a causal relationship between the maternal diet and neonatal microbial acquisition is yet to be established in humans.

Healthy dietary patterns that are high in fiber and low in fat are associated with higher microbial alpha diversity in adults [15]. Population-based metagenomic analysis indicates that the dietary features that are associated with higher alpha diversity (as measured by the Shannon Index) are frequent fruit and vegetable consumption along with polyphenol-containing tea, coffee, and red wine [16]. Conversely, dietary features associated with low alpha diversity are sugar-sweetened soda, whole fat milk, savory snacking, and a high total energy intake. Across the developed countries, the mean daily intake of fiber for pregnant women is 18 (SD 4.4) g, this is below the recommended ranges (21-28 g depending on country) [17]. Similarly, mean saturated fat intakes of 32.2 (SD 9.1) g/day were 8.5% to 16.5% above the recommended ranges (depending on country) [17]. In Australia, pregnant women have poor diet quality; they neither know nor meet the Dietary Guidelines for all 5 food groups [18-20], but they are motivated and would like further nutritional education [18].

### Objectives

The Healthy Parents, Healthy Kids (HPHK) study (Trial registration: Australian New Zealand Clinical Trials Registry, ACTRN12616000936426) is a prospectively registered open-label, parallel group, RCT of an educational perinatal dietary intervention targeting gut microbiota from the third trimester of pregnancy until 4 weeks after birth. The primary aim is to evaluate whether the dietary intervention alters alpha diversity of the infant gut microbiota 4 weeks after birth. Secondary aims are to evaluate the efficacy of the intervention in altering microbiota, inflammatory and stress profiles, epigenetic regulation, and maternal diet and well-being. The feasibility and acceptability of the study intervention will also be evaluated. The HPHK study intervention design couples pedagogical theory and educational design (focused on self-assessment and self-efficacy) with Behavior Change Techniques (BCTs) [21] to support efficacy and dietary adherence. A sound educational design is an important, yet seemingly overlooked consideration; first, it ensures that participants are able to *do* the target behavior, second, it helps to mitigate against confusing a true null effect with insufficient learning, and third, it safeguards the literature against spurious findings from poorly designed interventions.

## Methods

This protocol was written according to the SPIRIT 2013 statement [22]. See Figure 1 for the study flow diagram.

**Figure 1 figure1:**
[figure not shown]
Study flow diagram. Displays the timing for each activity of the randomized controlled trial.

### Primary Hypothesis

The dietary intervention will result in increased microbial diversity (Shannon index) in infants measured 4 weeks after birth, compared with the control group.

### Secondary Hypotheses

#### Microbiota

Using stool samples collected at follow-up, compared with the control group, the intervention group will have (1) dissimilarity in infant stool operational taxonomic units (OTU); (2) higher alpha diversity in maternal stool; (3) dissimilarity in maternal stool OTU; (4) increased relative abundances of genus *Prevotella* in maternal stool.

#### Diet

Women in the intervention group will (1) improve their diet in accordance with the Australian dietary guidelines; (2) consume a wider variety of foods; and increase intakes of (3) fiber, (4) prebiotic foods, and (5) probiotic foods compared with the control group, and these changes will be sustained throughout pregnancy. The intervention group will reduce intakes of (6) refined processed foods, (7) saturated fat, and (8) total energy compared with the control group. 

Further secondary hypotheses for other biological outcomes (ie, short chain fatty acid [SCFA] concentration, inflammation, stress, and epigenetic regulation) and study feasibility are listed in Multimedia Appendix 1.

### Primary Outcome Measure

A between-group difference in microbial alpha diversity, measured using the Shannon Diversity Index (which accounts for species richness and evenness) at follow-up (4 weeks after birth) in the infant stool samples.

### Secondary Outcome Measures

#### Infant Microbiota

Between-group differences in other diversity measures including inverse Simpson index (a measure of richness and evenness that is less affected by rare species compared with the Shannon index) and Chao1 (measure of species richness); observed species and phylogenic diversity (measure of diversity including phylogenetic distance); the relative abundance of OTU; beta diversity using measures of between-sample dissimilarity.

#### Maternal Microbiota

Between-group differences in the relative abundance of OTU; beta diversity using measures of between-sample dissimilarity in response to dietary intake. Baseline-adjusted between-group differences in alpha diversity indices (Shannon Diversity, Inverse Simpson, and Chao1); observed species and phylogenic diversity.

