### Data and Sample Collection

Data were collected at 4 time points: gestation week 26, 31, 36, and 4 weeks after birth (follow-up), as detailed in Table 1. Data collection included demographic, physical health and medications, mental health and social support, diet, lifestyle, and evaluative feedback. A probiotic food and drink questionnaire was administered at all time points for the intervention group, but only at baseline and follow-up for the control group to prevent the control group from becoming aware or prompted to increase intake of probiotic foods.

The study team were trained to collect baseline and follow-up anthropometrics and biological samples. Biological samples were collected as outlined in Table 2. Participants collected a baseline stool sample during gestation week 26, and a follow-up sample from themselves and their infant 4 weeks after birth. Stool samples were stored in the domestic freezer and transported on ice to the study visit scheduled during week 26 of gestation (or before week 29). The study team collected the follow-up samples during a home visit. Samples were transported to long-term storage (−80°C) on dry ice. At the conclusion of the study, stool samples were couriered on dry ice to the Australian Genomic Research Facility (AGRF) for DNA extraction and 16S rRNA sequencing. The V3-V4 hypervariable region of the 16S rRNA gene was amplified using a forward primer, 341F, 5’-CCTAYGGGRBGCASCAG-3’ and reverse primer, 806R, 5'-GGACTACNNGGGTATCTAAT-3'. Polymerase chain reaction amplicons were generated from approximately 100 ng of extracted DNA, and purified amplicons were sequenced using Illumina MiSeq, in accordance with the manufacturer specification and AGRF protocols.

**Table 1 table1:** Data collection schedule.

Measurement/instrument		Baseline (gestation week 26; mother)	Progress (gestation weeks 31 and 36; mother)	Follow-up (4 weeks postpartum)	
				Mother	Infant

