#### Secondary Outcomes

#### Gut Microbiota

Infant stool alpha diversity will be further analyzed using 4 other measures (Inverse Simpson, Chao1, phylogenic diversity, and observed species) using the same methods described for the primary outcome. All 5 alpha diversity measures will be analyzed for mothers adjusting for baseline measures. Further analyses will examine potential effect modification for storage duration, baseline, antibiotic, and medication use in accordance with Kraemer et al [54]. Between-group differences in the relative abundance of genus *Prevotella* will be analyzed using the same methods described for the primary outcome for infants and a baseline-adjusted method for the mothers.

A total of 2 beta diversity metrics will be calculated (Generalized UniFrac distances [55] and Bray-Curtis dissimilarity.) Group-based separation will be visually inspected using principal coordinates analysis and constrained ordination plots of these beta diversity metrics. Further plots will be created to inspect separation based on potential effect modifiers: mode of birth, antibiotics, sample collection week, and mode of feeding. Permutational multivariate analysis of variance (PERMANOVA) [56] with 999 permutations will be used on the beta diversity metrics to determine the statistical significance of group-based separation. In a secondary analysis, these PERMANOVA models will test for the aforementioned potential effect modifiers. Differential abundance testing with a false discovery rate correction will be performed to explore OTUs that are different between groups. The appropriate transformation and test will be determined in accordance with Weiss et al once library size is known [57]. For significant outcomes, the role of dietary change or probiotic or prebiotic supplementation in potentially mediating microbial outcomes will be examined.

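### Maternal beta diversity and OTU comparisons carry no baseline term, although maternal alpha diversity and Prevotella are baseline-adjusted and week-26 maternal stool is collected; the cost is precision, not validity

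*Protocol article*

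**What the plan says.** Under Secondary Outcome Measures, Maternal Microbiota, the Protocol article splits the maternal outcomes in two. The composition outcomes are "Between-group differences in the relative abundance of OTU; beta diversity using measures of between-sample dissimilarity in response to dietary intake". The diversity outcomes are "Baseline-adjusted between-group differences in alpha diversity indices (Shannon Diversity, Inverse Simpson, and Chao1); observed species and phylogenic diversity".

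The analysis text under Secondary Outcomes, Gut Microbiota, keeps the split:

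- **Alpha diversity:** "All 5 alpha diversity measures will be analyzed for mothers adjusting for baseline measures".
- **Prevotella:** "using the same methods described for the primary outcome for infants and a baseline-adjusted method for the mothers".
- **Beta diversity:** PERMANOVA with 999 permutations "will be used on the beta diversity metrics to determine the statistical significance of group-based separation". A secondary analysis tests "potential effect modifiers: mode of birth, antibiotics, sample collection week, and mode of feeding". Baseline composition is not in that list.
- **OTUs:** differential abundance between groups with a false discovery rate correction. The transformation and test are chosen once library size is known.

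The baseline material is collected. Data and Sample Collection states: "Participants collected a baseline stool sample during gestation week 26, and a follow-up sample from themselves and their infant 4 weeks after birth". Table 2 also shows maternal stool at both times and infant stool at follow-up only.

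**The concern.** Women differ in gut composition before any intervention. If those differences persist to 4 weeks after birth, a comparison of arms that ignores the week-26 sample leaves them in the error term. The plan accepts this reasoning for maternal alpha diversity and Prevotella but does not carry it over to composition.

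Dissimilarity in maternal OTUs is a named secondary hypothesis, and the proposed route to the infant runs through the mother's microbiota. A missed maternal signal would make a null infant result harder to interpret. With about 40 women per arm there is little precision to spare. A chance difference between arms at baseline would also carry through in part to the follow-up comparison.

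**Working it through.** **Inputs from the article.** Sample Size and Power gives 80 mothers, a difference of 0.25, SD 0.4, two-sided 5% and 80% power. Randomization gives 1:1 allocation. That is 40 per arm.

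**Input not in the article.** The correlation r between a maternal feature at week 26 and at follow-up. It is assumed to be 0.3, 0.5, 0.7 or 0.8.

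**Step 1: the plan's own figure.** Per arm, n = 2 × (1.960 + 0.8416)² × (0.4/0.25)² = 2 × 7.849 × 2.56 = 40.2, rounded up to 41, or 82 in total. With 40 per arm, power is 79.8% by the normal approximation and 78.8% by the t test. The stated 80 is reproduced closely enough. It concerns infant Shannon index; the article gives no power figure for maternal composition. It serves here only to fix 40 per arm.

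**Step 2: one maternal feature, with and without baseline.** Adjusting for baseline leaves residual variance (1 − r²) times the unadjusted variance. The sample that the unadjusted analysis needs for equal precision is larger by 1/(1 − r²). The difference detectable with 80% power is 2.8016 × √(2/40) = 0.63 SD unadjusted; adjusted, it is multiplied by √(1 − r²). The last column is power for an illustrative difference of 0.4 SD, which is 43% unadjusted.

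| Assumed r | Residual variance | Sample ratio | Detectable difference (SD) | Power at 0.4 SD |
|---|---|---|---|---|
| no adjustment | 100% | 1.00 | 0.63 | 43% |
| 0.3 | 91% | 1.10 | 0.60 | 47% |
| 0.5 | 75% | 1.33 | 0.54 | 54% |
| 0.7 | 51% | 1.96 | 0.45 | 71% |
| 0.8 | 36% | 2.78 | 0.38 | 85% |

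**Step 3: chance imbalance.** With 40 per arm, the difference between arms in a baseline mean has standard error √(2/40) = 0.22 SD. An imbalance of that size moves the unadjusted follow-up difference by r × 0.22, which is 0.07, 0.11, 0.16 or 0.18 SD at the four values of r. This averages to zero over repeated randomisations and the permutation p-value allows for it. In one trial, adjustment removes it.

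**Step 4: a multivariate check.** A permutation test was simulated on Euclidean distance with 10 features, 40 per arm, 199 permutations, 300 runs and a shift of 0.25 SD in every feature.

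| Assumed r | Power, follow-up only | Power, adjusted | Null rejection, follow-up only / adjusted |
|---|---|---|---|
| 0.3 | 63% | 69% | 5.0% / 4.0% |
| 0.5 | 59% | 79% | 4.3% / 4.3% |
| 0.7 | 70% | 94% | 4.0% / 5.7% |

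In this set-up follow-up-only power does not depend on r, so its spread is simulation noise; the standard error of each figure is about √(0.64 × 0.36/300) = 2.8 points. The pooled value is (63 + 59 + 70)/3 = 64%. The simulation treats the baseline slope as known, which slightly flatters the adjusted test. It supports the direction of the gain and shows that neither analysis inflates type I error.

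**The case against.** **The follow-up-only reading is inferred.** No sentence says that baseline stool will be left out of the maternal composition tests. The lead-in to the microbiota hypotheses, "Using stool samples collected at follow-up, compared with the control group, the intervention group will have", cannot settle it, because it also covers maternal alpha diversity and Prevotella, which are adjusted. The PERMANOVA sentence serves infants and mothers together, and infants have no baseline stool. The paragraph before it does name baseline among possible modifiers for the mothers' alpha diversity. This all stands. The point rests instead on the contrast drawn twice, in the outcome definitions and in the analysis text, and on the list of PERMANOVA terms nearest to the test, which omits baseline.

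**The OTU test is exploratory and partly open.** This is true and weakens that half of the point. Choosing a transformation and a test after seeing library size does not by itself add a baseline covariate.

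**A reader might infer bias or excess false positives.** The documents do not support that. Allocation is concealed and randomised, so a comparison of arms at follow-up is valid, and the simulated null rejection rates are near 5% either way.

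**The gain may be small.** The Discussion's statement of stability concerns alpha diversity, not composition, and the same paragraph cites a conflicting report of instability in pregnancy. Delivery also falls between the two samples. If r is near 0.3, adjustment removes only 9% of the variance.

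**Conclusion.** The point holds as one of efficiency and internal consistency. The article adjusts maternal alpha diversity and Prevotella for baseline but describes maternal beta diversity and OTU abundance as plain comparisons between groups, with the week-26 samples in hand. Across the assumed correlations of 0.3 to 0.8, using them would remove between 9% and 64% of the residual variance of a single feature. That range is an assumption throughout, and the multivariate gain depends on how well a few baseline axes capture stable differences between women.

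The stronger readings, that the plan expressly confines the maternal analysis to follow-up samples or that its test is biased, are not supported. The outcomes are secondary. The infant primary outcome and the sample size are untouched.

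**What to change.** For mothers only:

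1. **Beta diversity.** Fit the PERMANOVA of follow-up distances on arm conditional on a small number of leading principal coordinate axes of the baseline samples. Compute the axes with the same metric, fix their number in advance, and permute arm between women, since women were the units randomised.
2. **OTUs.** Include each OTU's transformed baseline abundance as a covariate in whichever differential-abundance model is chosen.
3. **Sensitivity analysis.** Keep the follow-up-only tests. They also cover women without a baseline sample, who could still qualify for the modified intention-to-treat set.
4. **Missing baseline samples.** State a simple rule in advance.

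Leave the infant analysis unchanged. The cost is analysis code, a sentence or two in the plan, and a few of the 78 residual degrees of freedom (80 − 2). No new samples are needed. The article reports that results are yet to be written, so the choice should be recorded before the maternal comparisons are run.

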#### Dietary Intake

Long-term (3-month) maternal dietary quality and variety are evaluated by applying the Dietary Guideline Index 2013 (DGI-13 scores) [23] to the validated Dietary Questionnaire for Epidemiological Studies v2 (DQES) [24], measured at baseline and 4 weeks after birth. DGI-13 scores include a total diet quality score and 13 subscores to evaluate each dietary guideline [25]. Daily macronutrients from the DQES are energy (kilojoules; kJ), protein (kJ), carbohydrate (kJ), fat (kJ), saturated fat (kJ) and fiber (grams). Time-related trends in short-term (2-week) diet quality and intakes of prebiotic and probiotic foods are evaluated using a version of the Simplified Dietary Questionnaire (SDQ) [26] modified to include prebiotic and probiotic foods. SDQ scores include a total diet quality score and comprises a dietary variety score and 9 subscores evaluating each guideline [25], along with 2 additional scores for prebiotic and probiotic food intake.

Further secondary outcome measures for other biological outcomes and study feasibility are listed in Multimedia Appendix 2.

